### Quality assurance

The procedures set out in this trial protocol, pertaining to the conduct, evaluation, and documentation of this trial, are designed to ensure that all persons involved in the trial abide by Good Clinical Practice [32] and the ethical principles described in the current revision of the Declaration of Helsinki [33]. The trial will be carried out in keeping with local legal and regulatory requirements.

### Statistics and data management

All analyses will be carried out on an "intent-to-treat" basis. However, attempts will be made to analyze "per protocol" and "intent-to-treat" populations separately, when statistically appropriate. For the purpose of "per protocol" analysis, two groups of 20 eligible patients completing the protocol will be considered. Drop-out patients are not to be replaced.

The target variables of this trial include laboratory values, outcome parameters and adverse events. The target variables are measured from study day -1 to study day 7. The differences of the laboratory values between study day -1 and 7 are tested with the paired t-test or, in case of uneven distribution, the Wilcoxon-test (2-sided) for within group comparison. The Mann-Whitney U test will be used to detect differences between treatment groups. The following statistical values will be calculated when appropriate: mean, standard deviation, 95%-confidence interval of the mean, minimum, lower quartile, median, upper quartile, maximum, valid number, frequency count, and percentage. The laboratory values will be counted according to their normal ranges (below normal, normal, and above normal). SAS software (Version 8.2) will be used for analysis.

All patient data (clinical and resource use) generated during the study will be recorded on the eCRFs provided by HealthEcon AG, Basel, Switzerland. These forms are specifically designed in Microsoft Office Access (Version: 1.01) to meet the data recording requirements of the clinical study protocol. Corrections of wrong entries will be recorded automatically. In addition, for any correction of data concerning "Adverse Events" or the primary target variable the reason for the correction must be entered. All data will be entered into a central database as recorded.

All data management activities will be done according to the current Standard Operating Procedures (SOPs) of HealthEcon AG.

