Before operation demographic data, medical history, physical examination, diagnosis, therapy, as well as comorbidities and concomitant medications are documented on day -1. Furthermore, routine laboratory measurements and substrate monitoring are carried out and documented (Table 2). On the day of surgery and following intubation for general anaesthesia, 500 ml milk containing test (melatonin; Helsinn Chemicals, Biasca, Switzerland) or placebo product (microcrystalline cellulose) (50 mg/kg BW) is administered via a standard gastric tube placed right after intubation of the patient. Clinical laboratory values (including chemistry, hematology, liver laboratory tests, and cytokines) and the substrates are measured on the day of operation and daily throughout the entire postoperative study period of 6 days. Clinical outcome parameters include infectious (pneumonia, wound infection, peritonitis, urinary tract infection, sepsis) as well as non-infectious (bilioma, bile fistula, pleural effusion, bleeding, circulatory insufficiency, renal insufficiency, wound dehiscence, intestinal obstruction/ileus, pulmonary embolism) complications. Sepsis is defined as the presence of at least 2 out of the following 4 criteria: (1) temperature >38°C or <36°C, (2) tachycardia >90/min, (3) respiratory insufficiency (1 out of 3 criteria: respiratory rate >20/min, hyperventilation with PaCO2 <32 mmHg or PaO2 <70 mmHg (spontaneous breathing) or PaO2/FiO2 <175 mmHg (mechanical ventilation), and (4) leukocytosis >12/nl or leukopenia <4/nl. Renal failure is defined according to RIFLE-criteria [31]. The schedule for all study related activities and data collection is listed in Table 2.

**Table 2 T2:** Flow chart, PORTAL study

**Phase**	Pre-OP day^1^	OP day^1^	Post-OP day 1–7^1^
**Study-day**	-1	0	1–7
Medical history	X		
Physical examination	X		
Inclusion/exclusion criteria	X		
Karnowsky index	X		
Patient information	X		
Patient informed consent	X		
Concomitant medication	X		X
Documentation of surgery (OPS code)		X	

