### Objectives and endpoints

The primary aim of this pilot study is to evaluate safety and tolerance of preoperative application of melatonin in patients undergoing operative procedures for partial liver resection. In addition, clinical parameters reflecting pathophysiological functions of the liver will be determined.

Data on clinical outcome (infectious and non-infectious complications) are collected as secondary endpoints to allow a power calculation for a randomized clinical trial aiming at clinical efficacy (Table 2).

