### Randomization and blinding

Randomization (1:1) will be performed by the algorithm programmed in specific computer software and a randomization list will be prepared. Briefly, "blocked randomisation" will be performed using blocks of four that will include equal packages of test product and control product with the order of treatments within a block being randomly permuted, thus ensuring treatment group numbers are evenly balanced at the end of each block. The random number sequence is chosen to start from 1001 and sets an ascending allocation order for the first four subjects. Similarly, treatment type is allocated to the next four patients in the order specified by the next randomly selected permutation. The process is then repeated. The randomization list will be prepared by the institution that is responsible for the packaging of the study products (test product, placebo), i.e. the Pharmacy of the University clinic of Heidelberg, and kept in safe and confidential custody at this institution.

Patients satisfying the enrolment criteria will receive an ascending serial number in the order of their enrolment. Patient numbers for patients who replace drop-outs will be assigned similarly.

Both study products, test (melatonin) and placebo product (microcrystalline cellulose), will be of same form and appearance (white powder in sachets) including the packaging material.

In addition to the trial medication, the clinical trial director (PS) will receive a set of sealed envelopes, one for each randomization number. An identical set of sealed envelopes will be held at the Pharmacy of the University clinic of Heidelberg. These envelopes contain information on the subject's trial medication and are to be opened only under circumstances in which it is medically imperative to know what the subject is receiving.

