### Adverse events

An adverse event (AE) is defined as any untoward medical occurrence in a subject administered a pharmaceutical product whether or not related to the investigational product including: new symptoms/medical conditions, new diagnosis, changes of laboratory parameters, intercurrent diseases and accidents, recurrence or worsening of pre-existing co-morbidities, increase of frequency or intensity of episodic diseases. A serious adverse event (SAE) is a life-threatening event resulting in death or significant persistent disability requiring subject hospitalization or prolongation of existing hospitalization. All AEs that occur after the subject has signed the informed consent document to participate in this evaluation of safety and tolerance of preoperative melatonin will be documented on the appropriate pages provided in the electronic Case Report Forms (eCRF). AEs must also be documented in the subject's medical records and must be monitored to determine outcome. The clinical course of the AE will be followed up until its resolution or normalization of changed laboratory parameters or until it has changed to a stable condition. SAEs must be reported using the "Serious Adverse Event" form provided in the eCRF. The initial report must be as complete as possible including details of the event and an assessment of the causal relationship between the event and the trial medication. The clinical trial director must also inform site monitor and data management in all cases.

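### The intention-to-treat rule covers the primary safety analysis, so any patient allocated but never dosed would stay in the safety denominator and pull the arms together

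*Protocol article*

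**What the plan says.** Protocol article, Statistics and data management, sets one population for everything: "All analyses will be carried out on an 'intent-to-treat' basis". The same section brings adverse events under that rule: "The target variables of this trial include laboratory values, outcome parameters and adverse events". Objectives and endpoints makes harm the main question: "The primary aim of this pilot study is to evaluate safety and tolerance of preoperative application of melatonin".

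A second population is offered conditionally: "However, attempts will be made to analyze 'per protocol' and 'intent-to-treat' populations separately, when statistically appropriate". It is limited to completers: "two groups of 20 eligible patients completing the protocol will be considered". The text names no set of treated patients.

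On timing, Randomization and blinding says: "Patients satisfying the enrolment criteria will receive an ascending serial number in the order of their enrolment". Table 2 places consent and the eligibility check on day −1. Methods/Design gives the product later: "On the day of surgery and following intubation for general anaesthesia".

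On recording, the Adverse events section documents "All AEs that occur after the subject has signed the informed consent document", yet defines an adverse event as occurring in someone who has been given a product. Table 2 marks adverse events on the operation day and days 1 to 7 only.

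**The concern.** In a superiority comparison of efficacy, keeping untreated patients in their allocated arm is the cautious choice, because dilution works against the new treatment. For harm the direction reverses: dilution makes the arms look alike, which favours the product. Here harm is the primary question, and the rule as written has no exception for it.

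The alternative set fails in a different way. It removes undosed patients, but it also removes dosed patients who did not complete, and Methods/Design lists intolerance and premature discontinuation among the causes of drop-out. One set can include the unexposed. The other can exclude those who tolerated the product badly. Neither consists of everyone who received it.

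**Working it through.** **No figure to reproduce.** The protocol gives 40 patients without an alpha, power, effect size or event rate.

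**Inputs from the protocol**
- 40 patients (Abstract), allocated 1:1 (Randomization and blinding): 20 per arm.
- Drop-out 10%, from mixed causes (Methods/Design): 0.10 × 20 = 2 per arm.

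**Assumptions**
- u, the share never dosed, is not stated. The range used is 0, 5% and 10%. The top value treats every drop-out as undosed.
- Adverse event rates if dosed, placebo against melatonin: 20% v 50%, with 10% v 30% and 30% v 70% as alternatives.
- Undosed patients have event rate q, and u is the same in both arms. That is reasonable, because losses before dosing occur under blinding and before exposure.

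**Formula.** The intention-to-treat rate in an arm is (1 − u) × p + u × q. Subtracting one arm from the other cancels u × q, so

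observed difference = (1 − u) × (p melatonin − p placebo).

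**Results for 20% v 50%, with q = 20% (the placebo-arm rate)**

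| u | Melatonin rate as analysed | Difference | Risk ratio |
|---|---|---|---|
| 0 | 0.500 | 0.300 | 2.50 |
| 5% | 0.95 × 0.50 + 0.05 × 0.20 = 0.485 | 0.285 | 2.43 |
| 10% | 0.90 × 0.50 + 0.10 × 0.20 = 0.470 | 0.270 | 2.35 |

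At u = 10% the other two pairs give 0.20 → 0.18 and 0.40 → 0.36.

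**If undosed patients have no events (q = 0).** At u = 10% the rates become 0.18 and 0.45. The difference is again 0.27, but the risk ratio stays at 0.45 / 0.18 = 2.50. The attenuation then shows only on the difference scale and in each arm's own rate.

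**Power, for scale only** (normal approximation, two-sided 0.05 assumed, u = 10%, q at the placebo-arm rate). The comparison is 18 dosed per arm against 20 per arm by intention-to-treat:
- 10% v 30%: 0.317 against 0.301
- 20% v 50%: 0.469 against 0.437
- 30% v 70%: 0.684 against 0.634

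The loss is about 2 to 5 points. Fisher's exact test gives 0.205 against 0.200, 0.359 against 0.338, and 0.609 against 0.493. The last gap is inflated by discreteness: with no undosed patients, 20 per arm gives 0.599, below the value for 18.

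**The case against.** The strongest reply is that u may be zero. Staff give one dose by gastric tube to an anaesthetised patient, so only withdrawals or cancellations before intubation remain. Cancelled surgery is not among the named drop-out reasons. Intolerance, and probably most loss to follow-up, would come after dosing. This stands, and it is why 27 points is an upper case.

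Allocation before the operation day is also an inference. Patient numbers follow enrolment order, and consent and eligibility fall on day −1, but Table 2 has no row for randomisation.

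Treated-patient sets are often left to an analysis plan. That would settle the matter if the protocol were silent. It states a rule for all analyses, and a plan that used a treated set for safety would depart from it.

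Patients whose operation was cancelled would have few or no postoperative laboratory values, so the dilution bears mainly on adverse events. This stands too.

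Two stronger readings are tempting, and the protocol supports neither:
- A reader might infer that recording events from consent makes pre-dose events count against melatonin. Such events arise under blinding in both arms, so they add noise rather than bias. The Adverse events section governs what is documented, not what is counted, and Table 2 has no adverse event mark on day −1.
- A reader might assume heavier dilution, such as 4 undosed of 20, which gives 0.80 × 30 = 24 points. That is 20% of an arm, twice the stated drop-out rate.

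**Conclusion.** The point holds as a defect in a stated rule, with low severity. As written, the primary safety comparison keeps any allocated but undosed patient, and the bias runs towards no difference. Its size is the fraction u of the true difference: nothing if everyone allocated is dosed, and at most a tenth if the whole 10% drop-out is undosed (30 points shown as 27). The 30-point excess is illustrative. The calculation assumes equal u and equal q in the two arms, and the mechanism assumes that numbers are assigned before dosing.

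A reader might conclude that the safety result will be materially biased. The protocol does not support that: it gives no undosed count, no power calculation and no adverse event threshold that a shift of this size could cross. The case for acting is that the correction is nearly free and protects the primary result should some patients go undosed.

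**What to change.** Replace the single population rule in Statistics and data management with two sentences:

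- The variables in the Safety and Tolerance block of Table 2 (adverse events and the laboratory values listed there) are analysed in all patients who received any study product, grouped by product received. Adverse events are counted from dosing onwards, and pre-dose events are listed separately.
- The secondary clinical outcome (infectious and non-infectious complications) is analysed by intention-to-treat.

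The laboratory values should move with the adverse events, since Table 2 classes them as safety variables. Leaving them behind would split the primary aim over two populations. An intention-to-treat laboratory comparison can be added as a supplement.

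Dropping undosed patients should not upset the balance between arms, because the reason for not dosing arises before exposure and under blinding. The number allocated but not dosed should be reported for each arm.

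The change needs no new patients, visits or measurements beyond the time of dosing and the onset time of events on the operation day. If every allocated patient is dosed with the assigned product, the treated set and the intention-to-treat set are the same.

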### Pharmacokinetics

The antioxidative effects of melatonin require concentrations that are much higher than endogenously produced plasma concentrations (peak plasma levels of approximately 100 pg/ml) [10]. Exogenous oral doses of melatonin >0.3 mg produce already supraphysiological levels in humans [11]. Orally administered melatonin is subject to extensive first-pass metabolism in the liver, and absolute bioavailability is reported to be approximately 15%, although highly variable [12,13]. Melatonin has an elimination half-life (t_1/2_) of 30–45 min [14-17] which is extended to approximately 100 min in cirrhotic patients [15]. In humans, the principal metabolite of endogenous as well as exogenous melatonin is 6-sulphatoxy melatonin [18].

Toxicity of melatonin is remarkably low. It was not possible to determine DL50 for melatonin since the highest possible does (800 mg/kg BW; limitation imposed by the solubility of the compound) failed to induce mortality in mice [19]. When melatonin was given to rats on gestation days 6–19 in very large doses (50–200 mg/kg BW, the doses equal to ~17.5 – 70 g/day) the maternal toxicity NOAEL (No Observed Adverse Effect Load) and LOAEL (Lowest observed adverse effect level) were 100 and 200 mg/kg/day, respectively, and the developmental toxicity NOAEL was >200 mg/kg BW [20]. No significant adverse effects were observed following administration of high doses (3 – 6.6 g/day) to eleven individuals for 15 to 35 days [21].

In the United States, the Food and Drug Administration (FDA) has designated melatonin as an orphan product sold as a dietetic complement with the only therapeutic indication in circadian rhythm disturbances in blind patients [22]. In most European countries this hormone is considered as a scientifically non-evaluated drug, therefore its sale is not allowed [4].

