### Trial rationale

Experimental data suggest that melatonin applied preoperatively would be suitable for prevention or prophylactic treatment of postoperative infectious and non-infectious complications induced by major surgical interventions. Exogenous, intragastrically applied melatonin as well as endogenously generated melatonin has been shown to promote healing of gastric ulcers in rats [23]. This antiulcer activity has been attributed to the ability of melatonin to stimulate enzymes that protect against oxidative stress [24,25]. Besides, orally-administered melatonin has been found efficient in reducing negative parameters of cholestasis and provided a hepatoprotective effect against the liver injury secondary to acute ligation of the biliary duct in rats [26,27]. Most recently we observed that rats gavaged with melatonin 2 h before warm ischemia/partial liver resection survive significantly longer than appropriate controls (unpublished data). Enzymes (transaminases) indicative for liver damage were also significantly reduced after preoperative melatonin following warm ischemia in both rats and pigs in a dose dependent manner (unpublished data). In clinical setting, melatonin has been shown to enhance neutrophil apoptosis after partial hepatectomy causing liver ischemia and reperfusion [28], thus eliminating the consequent active inflammatory response due to surgical injury [29]. Most recently, data from a randomized clinical trial has shown intravenous melatonin to decrease oxidative stress status and proinflammatory cytokines in human neonates undergoing surgery for congenital malformations [30]. However, the best administration route, the duration of treatment, the effective dose of melatonin, its exact role in the pathophysiology of surgical diseases, its pharmacological interactions and untoward side effects, as well as its long-term safety has not been fully established yet. Thus, this study has been designed to meet the need for a larger randomized controlled trial to confirm the suggested benefits of melatonin with the consideration of the current knowledge of its immunomodulatory effects.

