## Methods/Design

After the positive vote of the ethics committee of the Faculty of Medicine, Ruprecht-Karls University of Heidelberg, Germany, enrollment of the study subjects has been started in June 2007 in this randomized controlled double blind single center clinical trial as a pilot study on the safety and tolerance of preoperative melatonin application in patients undergoing major liver resection. Patients are considered for recruitment to the study according to inclusion and exclusion criteria (Table 1). The duration of the trial for each subject is expected to be 9 days, i.e. 1 day before operation (day -1), the day of operation (day 0) and the first 7 days following the operative procedure (postoperative days 1–7). Considering a recruitment rate up to 5 cases per month, the overall duration of the trial is expected to last approximately 8–10 months. A drop-out rate of 10% (due to non-compliance, intolerance, premature discontinuation, lost to follow-up, etc) will increase the total duration of trial to about 12 months. The actual overall duration of recruitment may vary due to the availability and consent rate of patients undergoing major liver resection.

**Table 1 T1:** Criteria of inclusion and exclusion of patients.

**Inclusion criteria**	**Exclusion criteria**
patients meeting all of the following criteria are considered for inclusion in the study:	patients with any of the following will not be included in the trial:
- scheduled for elective major partial liver resection of ≥3 liver segments for liver neoplasms	- patients <18 and >90 years
- written informed consent	- patients <50 and >120 kg
- adequate contraception is required for women with childbearing potential	- patients with severe, organ-specific disorders (e.g., liver or renal failure, acute pancreatitis)
	- patients undergoing emergency procedures
	- patients with expected intubation problems
	- pregnancy and/or lactation
	- history of hypersensitivity to the investigational product or to any drug with similar chemical structure or to any compound present in the pharmaceutical form of the investigational product
	- simultaneous participation in another clinical trial
	- mental condition rendering the subject incapable of understanding the nature, scope, and consequences of the trial
	No subject will be enrolled in this study more than once.

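### The only time contrast named for laboratory values is within-group, day -1 against day 7; no named test is tied to the daily values in between, where an acute effect of one dose is most likely to show

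*Protocol article*

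**What the plan says.** Statistics and data management lists laboratory values among the target variables and gives the measurement window: "The target variables are measured from study day -1 to study day 7". It then names one time contrast: "The differences of the laboratory values between study day -1 and 7 are tested with the paired t-test", or, if the distribution is unsuitable, "the Wilcoxon-test (2-sided) for within group comparison". The between-arm test has its own sentence: "The Mann-Whitney U test will be used to detect differences between treatment groups". That sentence names no day, no change score and no summary over days. The section also lists descriptive statistics and counts below, within and above normal range, again without days.

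The Abstract places clinical parameters of liver function among the primary endpoints, beside safety and tolerance. Table 2 schedules AST, ALT, LDH, CRP and IL-6 on day -1, day 0 and days 1-7.

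On the length of follow-up, Methods/Design first gives nine days per patient, ending with "the first 7 days following the operative procedure". Later in the same section, laboratory values are taken on the day of operation and "daily throughout the entire postoperative study period of 6 days".

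**The concern.** The trial tests one dose, given after intubation and before the liver is resected. The article's rationale is protection from acute injury. Its supporting animal evidence is an injury-marker result: "Enzymes (transaminases) indicative for liver damage were also significantly reduced after preoperative melatonin following warm ischemia". The drug is also short-lived: under Pharmacokinetics, "Melatonin has an elimination half-life" is followed by a range of 30-45 minutes, or about 100 minutes in cirrhosis.

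A contrast between the day before surgery and a week after it mainly asks whether values have returned to baseline. That is a fair recovery question, but it is not the question the rationale raises. A within-arm change also does not compare melatonin with placebo. If the between-arm test is read as using the same change score, a difference that arises early and fades by day 7 could go undetected although the daily samples contain it. If it is read as open, the day or summary could be chosen after the data are seen, across many analytes and nine days. The safety aim is touched in the same way, because a transient early rise under melatonin would not be tested either.

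**Working it through.** **Day count.** Day -1, day 0 and days 1-7 give 1 + 1 + 7 = 9, which reproduces the nine days stated in Methods/Design. Six postoperative days give 1 + 1 + 6 = 8, which does not. The nine-day total, Table 2 and the statistics section agree on day 7 as the last day; the six-day phrase stands alone.

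**Days tied to a named test.** The contrast uses 2 of 9 scheduled days. The other 7 (days 0-6, 7/9 = 78%) are tied to no named test.

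**Time since dosing.** Day 7 is 7 × 1440 = 10,080 minutes after dosing. That is 10,080/45 = 224 to 10,080/30 = 336 half-lives, or 10,080/100 = about 101 in cirrhosis. This describes drug clearance. It does not say how long a marker difference lasts.

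**What a day 7 contrast could cost.** The article states no alpha, effect size or SD, so there is no power figure to reproduce and everything here is illustration.

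Assumptions:
- 20 per arm (40 patients, 1:1) and two-sided 0.05.
- A day 1 effect d of 0.8 to 1.0 SD that halves every h days.
- Equal variances, and an equal correlation r of 0.5 to 0.7 between any two days, baseline included.

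Formulas:
- Effect on day t: d × 0.5^((t−1)/h).
- SD of the day -1 to day 7 change: √(2(1−r)), which is 1.00 at r = 0.5 and 0.77 at r = 0.7.
- SD of (mean of days 1-7 minus day -1): √((1+6r)/7 + 1 − 2r), which is 0.76 and 0.59.
- Power: Φ(effect/(SD × √(2/20)) − 1.96), ignoring the opposite tail, which adds about 0.01 at most in the rows below.

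Worked case, d = 0.8, h = 2, r = 0.5:
- Day 7: effect 0.8 × 0.5³ = 0.10; 0.10/0.316 − 1.96 = −1.64; power 0.05.
- Mean of days 1-7: effect 0.356; 0.356/(0.756 × 0.316) − 1.96 = −0.47; power 0.32.

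| Effect halves every | Power, day -1 to day 7 change | Power, mean of days 1-7 minus baseline |
|---|---|---|
| 2 days | 0.05-0.07 | 0.32-0.67 |
| 3 days | 0.09-0.17 | 0.46-0.85 |
| 7 days | 0.29-0.62 | 0.72-0.98 |
| no decay | 0.72-0.98 | 0.92-1.00 |

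The last row shows that part of the gain comes simply from averaging seven values. The rest depends on how fast the effect fades.

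**A second model, for a cleared enzyme.** Assume baseline 30 U/L, day 1 excess of 500 against 350 U/L, clearance half-life 18-48 h and log SD 0.6, and compare log levels by a z-test. On day 1 the log difference is ln(530/380) = 0.333, with power of about 42%. By day 7, 144 hours later, the excess has shrunk by 2^(−144/18) to 2^(−144/48). The levels are then 32.0 against 31.4 U/L up to 92.5 against 73.8 U/L. The log difference is 0.019 to 0.227, which is 6% to 68% of the day 1 value, and power is 5% to 22%.

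**The case against.** The strongest objection is that the quoted contrast is expressly a within-group test. The between-arm test is stated separately and no day is fixed for it, so a reader who infers that the plan compares the arms only at day 7 goes beyond the text. That stands: the most that can be said is that the day -1 to day 7 change is the natural reading, and that no other day or summary is named.

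A reader might also infer that the daily values are thrown away. The document does not support this. The descriptive statistics and normal-range counts are not limited to two days. Changes in laboratory parameters count as adverse events, and Table 2 records adverse events on day 0 and days 1-7. Early laboratory harm therefore has a reporting route, though not a prespecified comparison.

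The power figures rest on inputs that the article does not give, and they model parametric comparisons rather than the Mann-Whitney test. In the enzyme model as much as 68% of the effect may survive to day 7, and Table 2 variables such as albumin or creatinine need not follow that pattern at all. The trial is a pilot with safety and tolerance as its main aim, and it claims no power. All of this limits the size of the point. It does not remove it, because the Abstract makes liver parameters part of the primary endpoints and the one contrast that the article does fix suits them poorly.

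Finally, a reader might conclude from the six-day phrase that the day 7 test will have no data. That is unlikely: the same paragraph refers to Table 2 for the schedule, and Table 2 runs to day 7.

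**Conclusion.** The concern holds in a limited form. The article fixes one time contrast for laboratory values, within arm and between the two end days, and leaves the between-arm test without a day or summary. Seven of nine scheduled sampling days are therefore tied to no named test. That an effect would be concentrated in those days is an inference from the single dose, the short half-life and the acute-injury rationale; the article does not state it. The loss cannot be fixed as one number: under the first model's assumptions it runs from severe if the effect halves within 2 to 3 days to modest if it persists. The document does not establish that the trial would miss a real effect. It does establish that a better-matched comparison of samples already scheduled is available and is not named. The conflict between six and seven postoperative days is a separate wording slip that needs reconciling and adds little weight.

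**What to change.** For the injury and inflammation markers (AST, ALT, LDH, IL-6, CRP), prespecify one between-arm comparison that uses all scheduled postoperative days. Suitable choices are the postoperative area under the curve or the peak, compared by arm with the day -1 value as covariate, or a repeated-measures model over all days adjusted for day -1. Name a single choice before unblinding. State how the day 0 sample enters, since Table 2's fixed daily sampling time (for example 8:00) may place it before dosing. Keep day -1 against day 7 as a within-arm recovery summary.

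Separately, reconcile the six-day postoperative period in the running text of Methods/Design with the days 1-7 given earlier in that section, in Table 2 and in the statistics section, so that the last sampling day matches the analysis.

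The cost is a few sentences of analysis wording, slightly more programming and the need to commit to one summary. No samples are needed beyond those in Table 2.
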